#### Cardiorespiratory fitness

Cardiorespiratory fitness is considered a potential moderator to determine whether the effectiveness of the intervention is influenced by participants’ initial fitness levels. This is supported by previous research indicating that the effects of an affect-based exercise prescription were moderated by cardiorespiratory fitness levels [154]. To assess cardiorespiratory fitness, we use the Åstrand indirect test of maximal oxygen uptake (VO_2_max) [155], performed on a bicycle ergometer (Ergoselect 200), which is validated for measuring submaximal fitness [155]. Gender- and age-adjusted cutoffs categorize participants into low, moderate, and high fitness groups [155]. The reliability and validity of the Åstrand nomogram and its linear extrapolation for deriving VO_2_max have been well documented [156]. A submaximal fitness test is employed, as more than half of individuals with depression do not meet the primary or secondary criteria for maximal exertion in cardiopulmonary exercise testing [157].

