## Statistical methods

### Statistical methods for primary and secondary outcomes {20a}

Descriptive statistics are presented as means (M), standard deviations (SD), medians (Mdn), interquartile ranges (IQR), frequencies, and percentages (%). The primary outcome, device-based PA (Fibion^®^), and the secondary outcomes, depressive symptom severity (HAMD17, BDI-II) and health-related quality of life (SF-12), will be analyzed using linear mixed models (LMMs) with measurements at T1 and T2 as outcomes. Baseline values of the respective outcomes (T0) will be included as predictors, along with a baseline × time interaction to account for potential changes in baseline influence over time. Fixed effects will include group (CG, IG1, IG2), time (T1, T2), and the group × time interaction, with a random intercept for each participant. For the secondary outcomes, device-based PA at the corresponding time point will additionally be included as a predictor to examine whether changes in these outcomes are associated with PA. Estimated marginal means from the LMMs will be used to compare groups at each time point, with Dunnett’s adjustment applied for comparisons of each intervention group versus control.

Although randomization is expected to minimize baseline imbalance, any clinically relevant imbalances observed will be accounted for in adjusted analyses of the primary outcome.

Continuous predictors (e.g., age, BMI, baseline PA) will be examined for potential nonlinear effects and may be modeled using flexible approaches such as natural splines. Model assumptions, including normality of residuals and homoscedasticity, will be checked, and appropriate transformations or alternative methods will be applied if assumptions are seriously violated.

Baseline CRF will be tested as a moderator by including CRF and its interactions with group and time (CRF × group × time) in the LMMs. Models will first be run without CRF to estimate the overall intervention effect.

Implementation outcomes (reach, dose, fidelity, adaptation) and participant satisfaction will be summarized descriptively. Between-group differences (IG1 vs. IG2) will be explored using independent-sample *t*-tests. All statistical analyses are performed using SPSS and Jamovi [163], with the significance level set at *p*
$$\le$$ 0.05. The completed trial will be reported in accordance with the CONSORT 2025 statement [164].

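### The only interaction written out for the fitness moderator test, CRF × group × time in a T1/T2 model, tests whether moderation changes after T1, not whether fitness moderates the coaching effect

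*Protocol article*

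**What the plan says.** In the protocol article, the section on cardiorespiratory fitness under potential moderators gives the purpose of measuring fitness: "to determine whether the effectiveness of the intervention is influenced by participants’ initial fitness levels".

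Section {20a} on statistical methods sets the model. It uses "linear mixed models (LMMs) with measurements at T1 and T2 as outcomes". The T0 value is handled as a covariate: "Baseline values of the respective outcomes (T0) will be included as predictors". The base terms are given as: "Fixed effects will include group (CG, IG1, IG2), time (T1, T2), and the group × time interaction", with a random intercept per participant. Groups are to be compared through estimated marginal means at each visit.

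The moderator analysis is then specified in one sentence: "Baseline CRF will be tested as a moderator by including CRF and its interactions with group and time (CRF × group × time) in the LMMs". The model without CRF is fitted first for the overall effect. No other CRF contrast is described, and section {20b} plans nothing beyond what {20a} contains.

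**The concern.** The question about fitness has a simple null hypothesis: the difference between a coached arm and control does not depend on baseline CRF. In a model where both outcome visits come after coaching has started and T0 is a covariate, the coaching effect is carried by the group contrasts. Its moderation is therefore carried by CRF × group, at each visit or averaged over them.

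The one interaction the protocol writes out has a different null: that moderation is the same at T1 and at T2. A three-way term would carry moderation of change from baseline if T0 were a level of time, but here it is not.

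At stake is the reading of the result. A lasting fitness effect on coaching benefit would leave the named term null. A significant term would show only that moderation grew or faded between 10 and 36 weeks.

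**Working it through.** **Inputs from the protocol.** Three arms, 1:1:1; outcome visits T1 and T2; T0 as covariate; significance level 0.05; correlation between repeated measures 0.50; 87 participants required, 114 planned (29 and 38 per arm).

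**The plan's own figure.** The protocol states no power for the moderator test. Its sample size does reproduce, as a repeated-measures within-between interaction with k = 3 groups and m = 3 visits:

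- λ = f² · N · m / (1 − r) = 0.175² × 87 × 3 / 0.50 = 15.99
- df = (k − 1)(m − 1) = 4 and (N − k)(m − 1) = 168
- power = 0.903, matching the stated 90% at 87

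So r = 0.50 and these sample sizes are used below.

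**What the named term estimates.** Let δ_g(t) be the CRF slope in arm g (IG1 or IG2) minus the CRF slope in control, at visit t.

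- CRF × group × time: δ_g(T2) − δ_g(T1), 2 df
- CRF × group, averaged over visits: [δ_g(T1) + δ_g(T2)] / 2, 2 df

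If δ_g(T1) = δ_g(T2) = d, the first equals 0 and the second equals d. The three-way test then rejects at alpha for any d, any N and any correlation. This is algebra and needs no simulation.

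**Numerical check.** With complete data at two visits, the three-way F test is the CRF × group test on T2 − T1, and the averaged test is the CRF × group test on (T1 + T2)/2, both adjusted for baseline. Assumptions that the protocol does not supply: CRF standardised, the same slope difference in both coached arms, and a choice of SD scale. Two scales were used:

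- *Residual SD 1 at each visit, residual correlation 0.50.* Variance of the visit mean = (1 + 0.50)/2 = 0.75; variance of the difference = 2(1 − 0.50) = 1.00.
- *Outcome SD 1, r = 0.50 between all visits, then baseline-adjusted.* Residual variance = 1 − 0.25 = 0.75; residual covariance = 0.50 − 0.25 = 0.25. Variance of the mean = (0.75 + 0.25)/2 = 0.50; variance of the difference = 2(0.75 − 0.25) = 1.00.

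The scale therefore changes the power of CRF × group but not that of the three-way term.

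Rejection rates (4,000 runs per setting; repeat runs differ by a point or two):

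| Moderation | N | SD scale | CRF × group × time | CRF × group, averaged |
|---|---|---|---|---|
| 0.3 at both visits | 87 | residual | 5.2% | 23% |
| 0.5 at both visits | 87 | residual | 5.2% | 57% |
| 0.3 at both visits | 114 | residual | 5.1% | 30% |
| 0.5 at both visits | 114 | residual | 4.6% | 70% |
| 0.3 at both visits | 114 | outcome | 4.3% | 43% |
| 0.5 at both visits | 114 | outcome | 5.2% | 86% |
| 0.5 at T1, 0.25 at T2 | 114 | outcome | 18% | 61% |
| 0.5 at T1 only | 87 | residual | 45% | 17% |
| 0.5 at T2 only | 87 | residual | 44% | 16% |

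On the outcome scale at N = 87, a constant slope difference of 0.5 gives about 73% for CRF × group, and repeat runs at N = 114 reach 87%. Residual correlations of 0.3 and 0.7 left the three-way rate at 4.6% and 5.3%. A fitted random-intercept model gave 6.3% in 300 runs, which is compatible with 5%.

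**The case against.** The strongest reply is that the sentence describes what goes into the model, not which p-value decides. It speaks of CRF's interactions in the plural, and the bracket can be read as shorthand for the full factorial. CRF × group would then be present, and visit-specific moderation can be read from the fit. The section already compares groups visit by visit, so reading CRF the same way would be consistent. This stands as far as the model goes: the model can very probably answer the question.

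It does not clear the wording. The sentence says how moderation will be tested and writes out one interaction only. An analyst who takes the lower-order CRF × group coefficient from software with reference coding of time gets moderation at the reference visit alone. Nor is this merely detail left to an analysis plan, because the article itself fixes both the term and the visit structure.

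Other points also stand. The power of CRF × group rests on assumed slopes and on the SD scale. Moderation that changes over time is plausible here, since IG1 coaching ends at T1 while IG2 continues, and the three-way term has real power for that.

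A reader might go further and infer that the trial will report that fitness does not moderate the effect. The protocol does not say that a non-significant three-way term will be read that way, so this is conjecture.

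**Conclusion.** The point holds as a mismatch between the stated question and the term written out to test it. That term rejects about 5% of the time when fitness moderates the coaching effect equally at T1 and T2, and this figure depends on no assumption beyond the model structure in {20a}. CRF × group, averaged over visits, would have roughly 23–73% power at N = 87 and 30–87% at N = 114, for assumed constant slope differences of 0.3 to 0.5 SD per SD of CRF. The spread comes from slope and SD scale, and the protocol gives no basis for choosing within it.

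The scope is narrow. A reader might infer that the mixed model is misspecified or that the primary comparison suffers. Neither follows: CRF × group is probably in the model, and the overall coaching effect is estimated first without CRF. Only the moderator analysis needs correcting.

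**What to change.** In {20a}, name CRF × group as the moderation test, with CRF centred. Report the CRF-by-arm slope differences versus control at T1 and at T2 with confidence intervals, in line with the per-visit group comparisons already planned. A 2-df CRF × group test averaged over visits can serve as the overall test. Keep CRF × group × time as the secondary test of whether moderation changes after T1.

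The cost is a sentence of wording; the model, the data and the number of participants stay the same. There are two small downsides. The averaged test loses power when moderation is present at one visit only: with 0.5 at T1 only, N = 114 and the outcome SD scale, about 33% against 59% for the three-way term. That is why the visit-specific contrasts should carry the answer. Reporting both visits also adds a few contrasts: 2 arms × 2 visits = 4.

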### Interim analyses {21b}

No interim analyses are planned. All planned analyses (e.g., pre- to post-intervention effects, follow-up comparisons) are conducted after completion of data collection for the respective time points.

### Methods for additional analyses (e.g., subgroup analyses) {20b}

No additional or subgroup analyses are planned beyond those described for the primary and secondary outcomes.

### Methods in analysis to handle protocol non-adherence and any statistical methods to handle missing data {20c}

All study variables will be screened for missing data, outliers, and multicollinearity. Missing data patterns will be examined descriptively and visually, with Little’s MCAR test as a supplementary tool. The most plausible missing data mechanism (MCAR, MAR, or MNAR) will be inferred from these observations, study design, and theoretical considerations, and sensitivity analyses will be conducted to assess robustness [165]. If data are plausibly MCAR or MAR, appropriate imputation methods (e.g., multiple imputation) will be applied [166].

The primary analysis will follow the intention-to-treat (ITT) principle, including all participants as randomized and using the chosen imputation methods for missing data [166]. This approach estimates the effectiveness of the interventions under real-world conditions [167, 168]. A secondary per-protocol (PP) analysis, including only participants who adhered to the study protocol, will be conducted to estimate the intervention effect under ideal adherence [167].

### Plans to give access to the full protocol, participant-level data, and statistical code {31c}

The full study protocol can be made available upon reasonable request to the study sponsor. Access to the participant-level dataset and statistical code is not granted, as participants are not asked to provide consent for broader data sharing beyond the scope of the PACOUTPAT study. According to the terms outlined in the informed consent form, data may not be used for scientific purposes other than those explicitly stated in the approved study protocol.

## Oversight and monitoring

### Composition of the coordinating center and trial steering committee {5d}

PACOUTPAT is conducted as a single-center trial at the Sonnenhalde AG Psychiatric Clinic. The study is implemented by the Department of Sport, Exercise and Health (DSBG) of the University of Basel at the Sonnenhalde AG site.

The sponsor-investigator (MG) from the University of Basel is responsible for the overall coordination and quality assurance of the trial, including implementation in accordance with the protocol, data management and analysis, staff instruction, and dissemination of findings. Day-to-day trial operations are led by an affiliated doctoral student (CS) who oversees participant recruitment, data assessments, and intervention delivery. The doctoral student is supported by a research assistant who assists with recruitment, data collection, and communication with patients. PA coaches, all with a background in sport and exercise science, are trained by the doctoral student and deliver the intervention according to standardized procedures. The co-principal investigator ([name], chief physician of Sonnenhalde AG) is responsible for the implementation of clinical treatment and the supervision of patients. Furthermore, he ensures favorable recruitment conditions by integrating the intervention into treatment as usual and establishing effective communication between clinic staff and DSBG personnel. Clinic staff support recruitment by informing eligible patients about the study and encouraging contact with the research team.

The study team maintains structured communication through the following:Weekly to monthly meetings between the sponsor-investigator and the doctoral studentWeekly to biweekly meetings between the doctoral student and the research assistantWeekly to monthly meetings between the doctoral student or research assistant and the PA coachesWeekly meetings between the doctoral student or research assistant and the clinic staff

Additionally, an annual team meeting is held with the broader research team, including the sponsor-investigator, co-principal investigator, doctoral student, research assistant, PA coaches, and co-authors, to review study progress and coordinate next steps.

### Composition of the data monitoring committee and its role and reporting structure {21a}

The Department of Sport, Exercise and Health (DSBG) is fulfilling the monitoring duties associated with the present trial. Data monitoring is overseen by the secretary of the Psychosocial Health and Physical Activity Research Unit at the DSBG. A monitoring visit at 12 months and a close-out visit are performed according to the monitoring plan. Electronic files (and their backups) and other documents containing participant data are kept accessible and monitored. The sponsor answers all questions that arise from the monitoring procedures.

### Adverse event reporting and harms {22}

Adverse events are systematically recorded at both post-intervention and follow-up assessments. In the event of a serious adverse event, documentation is completed and reported to the study sponsor within 24 h. Additionally, PA coaches monitor participants throughout the intervention period and report any adverse events directly to the research team for initiation of documentation.

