## Trial design {8}

This study is a single-center, three-arm randomized controlled trial (RCT) with an allocation ratio of 1:1:1. It includes two intervention groups (IG1, IG2) and one control group (CG) and follows an open-label design. The trial is conducted in collaboration between the Sonnenhalde AG Psychiatric Clinic, Riehen, Switzerland, and the Department of Sport, Exercise and Health (DSBG) at the University of Basel, Basel, Switzerland.

The intervention is delivered in an outpatient setting, recruiting patients from day clinics of the Sonnenhalde AG. Assessments are conducted at three time points: (a) baseline (T0), (b) post-intervention (T1, 10 weeks after baseline), and (c) follow-up (T2, 36 weeks after baseline). The follow-up period of 26 weeks after post-intervention ensures alignment with prior comparable studies [77–79]. All assessments are conducted on-site at the day clinics.

An overview of the study design is provided in Fig. 1. The protocol is designed in accordance with the SPIRIT 2025 statement for interventional trials [80].

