Sessions 4 to 9 alternate between attending structured PA sessions and reflective sessions. These reflective coaching sessions involve evaluation of experiences, discussing whether specific activities should be continued or adapted, and planning future participation to optimize enjoyment and fit with individual preferences.

All 10 coaching sessions are conducted face-to-face in the participant’s personal environment to maximize individual support and real-world applicability. Each session is scheduled to last approximately 60 min.

To further facilitate behavior change, the coaching is supported by a wearable smart ring, adhering to 12-point WATCH (Wearable Activity Tracker Checklist for Healthcare) guidelines [92]. Specifically, the Oura Ring (Generation 3; Ōura Health Oy, Finland) is used. The lightweight device (4–6 g) includes a 50-Hz triaxial accelerometer, NTC thermistor, and photoplethysmograph to continuously measure movement, body temperature, heart rate, heart rate variability, and respiration [93]. The ring is worn on the nondominant hand (index, middle, or ring finger). The device comes with a 6–7-day battery life and uploads data to both a smartphone app and a secure cloud dashboard. This allows coaches to monitor participants’ PA levels, energy expenditure, and sleep patterns. Participants in IG1 continue to wear the ring after the end of the 10-week coaching program until follow-up.

### Intervention Group 2

Participants assigned to IG2 receive the same 10-week interest- and experience-based coaching as IG1 and also continue to wear the Oura Ring until follow-up. However, unlike IG1, IG2 remains in contact with the coach for an additional 6 months (26 weeks) to receive cognition-based coaching aimed at promoting sustainable behavior change.

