During this phase, biweekly phone calls are conducted to assess participants’ PA habits and adherence to their routines, offering support if difficulties arise. These brief (~20-min) phone sessions focus on applying evidence-based behavior change techniques (BCTs) to reinforce long-term habit formation [94]. Strategies include structured activity planning, identifying and overcoming barriers, leveraging social support, and relapse management. The goal is to enhance self-regulation and resilience, ensuring that participants maintain their achieved activity levels beyond the initial intervention period. A detailed description of the intervention procedures is provided in the Intervention Guide, which is available as Additional file 1.

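### Coach reporting gives IG1 and IG2 an adverse-event route that controls lack, so per-arm counts may be inflated in the coached arms if visit recording is incomplete

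*Protocol article*

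**What the plan says.** The section Adverse event reporting and harms {22} sets two routes. The first covers every participant: "Adverse events are systematically recorded at both post-intervention and follow-up assessments". By Trial design {8} these visits fall at weeks 10 and 36, so they look back over 10 and 26 weeks. The second is added to it: "PA coaches monitor participants throughout the intervention period and report any adverse events directly to the research team", and such a report starts the documentation. Serious events have their own rule, which names no arm: "In the event of a serious adverse event, documentation is completed and reported to the study sponsor within 24 h".

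Only two arms have a coach. For the 10-week program in IG1 and IG2, Intervention description {11a} says "All 10 coaching sessions are conducted face-to-face". IG2 then has 26 further weeks in which "biweekly phone calls are conducted to assess participants’ PA habits and adherence to their routines". The section Control group gives controls usual day-clinic treatment and a printed booklet. No interim enquiry about adverse events is described for them.

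The article is not consistent on how long the intervention lasts. Trial design {8} labels week 10 post-intervention and the following 26 weeks follow-up. Intervention description {11a} speaks of support for up to 36 weeks, made up of 10 plus 26.

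The article states no between-arm analysis of adverse events. Statistical methods {20a} commits the trial to reporting under CONSORT 2025.

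**The concern.** Coached participants can enter the adverse-event record in two ways and controls in one. If the visit enquiry misses events, a count per arm reflects how closely each arm was watched as well as how much harm occurred. Minor injuries and complaints are the likeliest to be affected: a coach may hear of one within days, whereas at T2 it may lie up to 26 weeks back.

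Harms are part of judging a program whose aim is to make patients more active. The distortion would run against coaching and could pass for a safety signal. If the source of each event is not recorded at collection, a later analysis may be unable to separate what the visits elicited from what only a coach knew.

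**Working it through.** The plan gives no adverse-event rate and no figure to reproduce. The check counts recording opportunities and then asks what unequal capture does when true risk is equal.

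**Inputs from the article**
- Visits: T1 at week 10 and T2 at week 36 (Trial design {8}).
- Coach sessions in weeks 0 to 10: 10 in IG1 and IG2 (Intervention description {11a}).
- Calls in weeks 10 to 36, IG2 only: one every two weeks for 26 weeks, so 26/2 = 13 (same section).

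**Opportunities over 36 weeks**
- CG: 2 visits.
- IG1: 2 + 10 = 12.
- IG2: 2 + 10 + 13 = 25 if the calls count as coach monitoring; 2 + 10 = 12 if the coach's reporting duty ends at week 10.

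**Assumptions (none is in the documents)**
- The true event rate is the same in all arms and spread evenly over 36 weeks.
- A share s of events is recorded through T1 and T2.
- While a coach is reporting, the coach detects a share c, independently of the visits.

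**Formulas**
- Share recorded while a coach is reporting: u = 1 − (1 − s)(1 − c).
- CG records s.
- IG1 records (10u + 26s)/36.
- IG2 records u on the 36-week reading, and the same as IG1 on the 10-week reading.

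**Results**

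| s | c | u | IG1/CG | IG2/CG, 36-week reading |
|---|---|---|---|---|
| 0.5 | 1 | 1 | (10 + 13)/36/0.5 = 1.28 | 1/0.5 = 2.0 |
| 0.8 | 1 | 1 | (10 + 20.8)/36/0.8 = 1.07 | 1/0.8 = 1.25 |
| 0.6 | 0.6 | 0.84 | (8.4 + 15.6)/36/0.6 = 1.11 | 0.84/0.6 = 1.40 |
| 0.8 | 0.3 | 0.86 | (8.6 + 20.8)/36/0.8 = 1.02 | 0.86/0.8 = 1.075 |
| 0.4 | 0.9 | 0.94 | (9.4 + 10.4)/36/0.4 = 1.38 | 0.94/0.4 = 2.35 |
| 1.0 | any | 1 | 1.00 | 1.00 |

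On the 10-week reading, IG2/CG equals the IG1/CG column. The first two rows set c = 1 to represent near-complete coach detection. The next three vary both shares and show how far the ratio depends on them.

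**After the fix.** If only events elicited at T1 and T2 are compared, each arm records s and every ratio is s/s = 1.00. This holds as long as coach contact does not change what participants report at the visits.

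**The case against.** The strongest reply is that no biased analysis is stated. Adverse events are not a listed outcome, and the statistical section gives no model or test for them. How harms are tabulated usually belongs in the full protocol or the analysis plan, and the case report form is not shown, so a source field may already exist. This stands in part: it rules out saying that a planned comparison is biased or that the sources cannot be separated. It does not remove the point, because the unequal collection rule is stated in the article and will affect any table of harms by arm that pools both routes. That such a table will be produced is my assumption.

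A reader might infer that controls are unobserved between visits and counted only by recall. The text does not support that. It says events are recorded systematically at the visits, and recall is only an inference from the 10- and 26-week windows. Baseline falls 2 to 4 weeks into a 12-week day-clinic treatment, so all arms are still in the clinic for about 12 − 4 = 8 to 12 − 2 = 10 weeks after it. The study team also meets clinic staff weekly. No adverse-event task is stated for those contacts, and they do not cover the 26 weeks after T1, but controls are not out of sight in the first phase.

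A reader might also infer a built-in gradient from CG through IG1 to IG2. That depends on which meaning of intervention period applies, and the article supports both. The description of the IG2 calls covers activity habits, adherence and difficulties, and does not mention asking about adverse events.

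Finally, the 24-hour rule for serious events names no arm, so the problem concerns mainly non-serious events.

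**Conclusion.** The point holds in a limited form. The article gives the coached arms an adverse-event route that controls do not have. If recording at T1 and T2 is incomplete, per-arm counts may overstate events in IG1 and IG2 relative to CG at equal true risk.

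The size cannot be derived from the documents. With 50% to 80% captured at visits, coaches detecting nearly everything and events spread evenly, IG1/CG is about 1.28 to 1.07. IG2/CG is 2.0 to 1.25 on the 36-week reading and equals IG1/CG on the 10-week reading. It would be wrong to apply 2.0 to 1.25 to coaching in general: over the whole trial that range fits only an arm coached for all 36 weeks, and IG1 is coached for 10 of them. Less complete detection by coaches shrinks the ratios, and complete visit recording brings them to 1.00.

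The effect is on descriptive harms reporting. The primary and secondary outcome analyses are untouched. The change is still worth making, because it is cheap and the source of an event is hard to reconstruct later.

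**What to change.** - Record the source of each adverse event: T1/T2 assessment, coach, or other.
- Base any between-arm harms table on events elicited with the same questions at T1 and T2 in all three arms.
- List events known only through coaches separately for IG1 and IG2, without comparison to CG.
- State whether the intervention period in the adverse-event section ends at week 10 or includes the 26-week call phase, so that the coach-only listing can be read correctly.
- Leave coach reporting and serious-event reporting for safety oversight unchanged.

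The cost is one field in the electronic case report form and a sentence or two on tabulation, with no extra visits or staff. Data collection runs to September 2027, so most events can still be classified as they arise.

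There are two drawbacks. The comparative table will leave out events known only to coaches, which is why the separate listing is needed. Some differential reporting may also remain, because the visits are unblinded and participants who have already discussed an event with a coach may mention it more readily.
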